### Secondary indicator

#### Adverse event

Abnormal conditions in the observation period, such as needle dizziness, broken needles, bleeding and hematoma, will be recorded. The occurrence time, cessation time duration, correlation with acupuncture, the measures taken and outcomes of adverse events will be recorded too. Serious adverse events during the observation will be reported promptly.

### Participant timeline

As a dynamic registry design, we plan to stick to the registry for at least 2 to 5 years. The tolerance range of time is 3 days around the follow-up point. If the patient does not return after the last visit, follow-up is done by phone within 1 week. At least ensure follow-up at these three time points,1 week, 4 weeks and 12 weeks. Contents of follow-up: whether there is a recurrence, whether there is back pain related surgery, whether there is any other treatment.

### Sample size

Currently, there is no valid sample size calculation method for registry studies. According to experience, the principle of sample size estimation in multivariate analysis of variance is 5–10 times the number of variables. Our preliminary research variables are no more than 20, so the sample size of the study is 1000–2000, taking the maximum value, our sample size is set at not less than 2000. To ensure better data representation and reflect the diversity of acupuncture operations, we will recruit no less than 9 centers, at least 3 acupuncturists in each center, that is, at least 27 acupuncturists.

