**Methods:**

A prospective, multi-center and dynamic registry study. All acupuncture related information will be collected through a high-quality structured network platform. Patients with CLBP included in the study met the following criteria: age from 16 to 80 years, using acupuncture as a main therapy and voluntarily signing the informed consent. At least 2000 patients, 27 acupuncturist, and 9 medical centers will be recruited under actual clinical settings at the first stage. Numeric rating scale (NRS), Oswestry Disability Index (ODI) and Effective rate will be measured in pain and functional disability assessment, respectively, as the primary outcome. Evaluation index will be collected at the baseline and follow-up in 1, 4, 12 weeks after the last visit. Hierarchical models and regression analysis will be used to explore the key factors affecting acupuncture effectiveness. Effects between propensity matching groups (Traditional Chinese acupuncture style vs Microacupuncture style, Local acupoint selection vs Non-local acupoint selection, Single Acupuncture vs Combined therapy) will be compared.

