### Statistical methods

#### Missing data

Although we have internal quality control methods to ensure data integrity, follow-up nonresponse shall be an inescapable challenge in a prospective observation study. Fortunately, we will recruit experienced physicians with stable patient population (at least 5 years of acupuncture experience or middle and senior titles), so the bias for lack of follow-up could be controlled partially. Real-time monitoring of the electronic network platform shall control missing data less than 20%. According to the classical rules of missing classification, follow-up nonresponse belongs to missing not at random (MNAR) [40]. Multiple imputation invented by Rubin shall be adopted to process missing data [41].

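### The stated sample-size rule gives 100–200 patients, not 1000–2000, so it does not yield the target of 2000

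*Protocol article*

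**What the plan says.** The Sample size section of the protocol article first says that no valid calculation method exists for registry studies. It then turns to a rule of thumb: "the principle of sample size estimation in multivariate analysis of variance is 5–10 times the number of variables". The input follows, and the result is drawn from it directly: "Our preliminary research variables are no more than 20, so the sample size of the study is 1000–2000". The upper end becomes the target: "taking the maximum value, our sample size is set at not less than 2000".

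The same section then sets the numbers of sites and practitioners, "we will recruit no less than 9 centers, at least 3 acupuncturists in each center". The reason given for these is representation and the diversity of acupuncture practice. They do not enter the patient calculation. The Methods part of the abstract repeats the target: "At least 2000 patients, 27 acupuncturist, and 9 medical centers will be recruited".

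**The concern.** The derivation has one multiplication, and its result does not match its two inputs. The section offers no other argument for the number of patients, and the abstract carries 2000 as a headline figure. If the product is wrong, the target stands without a stated justification, and a reader cannot tell which of three things happened: the product was miscalculated, the multiplier or the variable count was misstated, or a step was left out. Nor does the rule tell the reader what 2000 patients deliver for the outcomes the registry will report.

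**Working it through.** **Inputs, all from the Sample size section**
- Multiplier: 5 to 10 patients per variable.
- Number of variables: at most 20.
- Stated result: 1000–2000, with the maximum as the target.

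**The plan's own figure**

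N = multiplier × number of variables.
- Lower end: 5 × 20 = 100, against the stated 1000.
- Upper end: 10 × 20 = 200, against the stated 2000.
- Ratio: 1000/100 = 2000/200 = 10 at both ends.

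Twenty is an upper bound, so fewer variables would widen the gap.

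**What the rule would need in order to give 1000–2000**
- With the multiplier as stated: 1000/5 = 2000/10 = 200 variables.
- With 20 variables: 1000/20 = 50 to 2000/20 = 100 patients per variable.

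**Can another figure in the article supply the missing factor?**

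| Variant | Result |
|---|---|
| Inflated for 20% missing data (limit in the Missing data section): N/0.8 | 125–250 |
| Two groups: × 2 | 200–400 |
| Three named comparisons of two groups: × 6 | 600–1200 |
| × 9 centres | 900–1800 |
| × 9 centres, then /0.8 | 1125–2250 |
| × 27 acupuncturists | 2700–5400 |

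None gives 1000–2000. Two constructions do, but each needs an input that the article does not state:
- Reading the rule as 5–10 events per variable with a 10% event rate: 100/0.1 = 1000 and 200/0.1 = 2000. At other assumed rates the range moves to 2000–4000 (5%), 500–1000 (20%) or 200–400 (50%).
- Nine centres with 10% loss: 900/0.9 = 1000 and 1800/0.9 = 2000.

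**Illustration of a usable justification**

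The article gives neither an expected effective rate nor an intraclass correlation (ICC), so both are assumptions here: a rate of 60%, and an ICC by acupuncturist of 0.01 to 0.10. Also assumed are all 2000 patients analysed and equal loads across exactly 27 acupuncturists, that is 2000/27 = 74.07 patients each.

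- Design effect: DE = 1 + (74.07 − 1) × ICC.
- 95% half-width = 1.96 × √(0.6 × 0.4 × DE / 2000).

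| ICC (assumed) | DE | Half-width, percentage points |
|---|---|---|
| 0 | 1.00 | ±2.1 |
| 0.01 | 1.73 | ±2.8 |
| 0.05 | 4.65 | ±4.6 |
| 0.10 | 8.31 | ±6.2 |

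The article sets 27 as a minimum. More acupuncturists for the same 2000 patients would lower the design effect.

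**The case against.** The strongest reply is that the slip is harmless. The error makes the rule look more demanding than it is, the target is ten times the rule's correct maximum, and no endpoint, analysis or enrolment figure depends on the faulty step. That stands as far as enrolment goes. A reader might infer that the registry is too small; the article does not support this, and the error points the other way. The reply does not make the stated range correct, and it leaves the target without a derivation.

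A second reply is that a journal article condenses, and that a power or precision statement for each comparison may sit in the full protocol or the analysis plan. That is fair, and its absence is not the point here. The article does print a derivation, with both inputs and the result, and an unseen document cannot make that product true.

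Three further readings are tempting but not supported:
- **That Table 1 disproves the limit of 20 variables.** The table lists registry metadata, including names, contact details and identity numbers, which are not model variables. It does not show how many variables will be modelled. Even a count of about 58 items would give only 5 × 58 = 290 to 10 × 58 = 580.
- **That the propensity-matched comparisons are shown to lack power.** This would need a number of pairs and a standard deviation, and the article gives neither. The 10-point ODI threshold in the Effective rate section classifies individual patients; it is not a between-group target.
- **That 2000 was chosen for representation.** The article gives that reason for the centres and acupuncturists, not for the number of patients.

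**Conclusion.** The concern holds as a point of arithmetic. The stated rule and input give 100–200, the article states 1000–2000, and the discrepancy is a factor of ten at both ends. This rests only on figures printed in the Sample size section and needs no assumption. The rule therefore does not yield 2000, and it is the only basis given for that number.

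The finding goes no further. It does not show that 2000 is inadequate, or where the slip lies. The half-widths in the working illustrate what a justification could look like; they depend on the assumed rate, ICC and equal loads, and are not evidence against the target.

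**What to change.** Keep the target of at least 2000 and rewrite the paragraph in the Sample size section.

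1. Correct the product to 100–200. If the multiplier or the variable count was misstated, or a step was omitted, correct or state that instead.
2. Replace the derivation with the actual basis for 2000. The sponsor must confirm what it was; a reviewer should not supply a reason.
3. Preferably, express that basis as the 95% confidence interval half-width that 2000 patients give for the effective rate, allowing for clustering by acupuncturist. Show it over a range of ICC values, with the rate and the ICC labelled as assumptions.

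The cost is one paragraph and no extra patients. The downside is that the rule of thumb no longer supports the target, and the stated precision is less favourable once clustering is counted: under the assumptions above, ±2.8 to ±6.2 points instead of ±2.1.

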To develop an international registration platform of CLBP for acupuncture therapy;To identify the key factors affecting the clinical effectiveness of acupuncture in treating CLBP from the perspective of acupuncture implementation and physicians;To analyze population characteristics and subtypes of CLBP suitable for acupuncture.

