### Data elements and collection methods

All information will be collected through a specific network platform for acupuncture therapy and put on record in a paper version (http://www.amreg.org/). The main data elements include information of medical centers and acupuncturists, characteristics of patients with CLBP, acupuncture operation details, outcomes and safety information. Informed consent requires scanning and uploading. The names of diseases related to chronic back pain are identified by International Classification of Diseases (ICD-10,2010 Version) [37]; TCM syndromes are confirmed by Classification and codes of diseases and *ZHENG* of traditional Chinese medicine (GB/T 15657–1995) [38]. The acupuncture point vocabulary adopts the WHO Standard Acupuncture Point Locations in the Western Pacific Region (A WPRO Publication, 2008) [39]. All data elements will be collected using the established terminology specifications, data dictionaries.

Most of the data use structured information entry, allowing free text entry to a certain extent. Platform support Pinyin code retrieval and input and fuzzy matching input to ensure the standardization of registration information and facilitate the statistical analysis of data. Under the premise of ensuring the necessary information, entries should be as little as possible to minimize the burden on clinicians. Specific entries and variables are available in Table 1.

**Table 1 Tab1:** Metadata of main items and variables

Major data sources	Main items	Property	Main variables and labels
Medical Centre	Institutional background	Indispensable	Medical Organizations, Location and hospital attributes, Medical institution level
	Registration of contribution	Indispensable	Number of recruited practitioners, Number of enrolled patients
Physicians	Demographic Information	Indispensable	Name, Age, Gender, Place of residence, Contact information, Educational background
	Practitioner background	Indispensable	Medical Organizations, Years of employment, Professional qualification (senior or intermediate professional title)
Patients	Demographic Information	Indispensable	Name, Age, Gender, Nationality, ID number, Residence, Occupation, Marriage status. Educational Qualifications, Contact information

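### Physician factors are an objective, but the acupuncturist is not a level in the planned models, and the minimum of 27 acupuncturists is not sized for those factors

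*Protocol article*

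**What the plan says.** The second objective in the Background section is "To identify the key factors affecting the clinical effectiveness of acupuncture in treating CLBP from the perspective of acupuncture implementation and physicians". Table 1 (Data elements and collection methods) collects the physician's age, gender, residence and education, and under practitioner background "Medical Organizations, Years of employment, Professional qualification (senior or intermediate professional title".

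The Sample size section takes as its principle that "the principle of sample size estimation in multivariate analysis of variance is 5–10 times the number of variables". With at most 20 variables it arrives at a range of 1000 to 2000 patients, and its final choice reads "taking the maximum value, our sample size is set at not less than 2000". The numbers of centres and acupuncturists are set in a sentence of their own: "we will recruit no less than 9 centers, at least 3 acupuncturists in each center, that is, at least 27 acupuncturists". The reason given for them is that the data should be representative and show the variety of acupuncture practice; the variable rule is not applied to them. The abstract presents all three counts as first-stage minimums: "At least 2000 patients, 27 acupuncturist, and 9 medical centers will be recruited under actual clinical settings at the first stage".

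The Analytic approach section plans linear regression on the propensity score and baseline characteristics, logistic regression on baseline factors, and conditional logistic regression for 12-week predictors. It also plans hierarchical models based on pain grade, medical centre, age group, gender, TCM syndrome and disease class. The acupuncturist appears in none of these.

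**The concern.** Years in practice, professional title and the other physician attributes are constant over all patients of one acupuncturist. Information on them comes mainly from the number of acupuncturists, whatever the number of patients. Patients of the same acupuncturist also tend to have correlated outcomes. A model without that level treats each of the 2000 patients as a separate piece of evidence about the physician. Two things are then at stake:

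- Physician factors could be named as key by chance, because their standard errors are too small.
- A reader could take the 2000 patients as assurance of a precision for physician factors that the design does not have.

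**Working it through.** **Plan's own figures.** 9 × 3 = 27 acupuncturists reproduces. The 2000 does not follow from the stated rule, since 20 × 5 = 100 and 20 × 10 = 200. That is a separate error, and correcting it would not settle how many acupuncturists the second objective needs. The check below takes 2000 and 27 as given.

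**Inputs from the protocol article.** 2000 patients and 27 acupuncturists (Sample size), so m = 2000/27 = 74.07 patients each, assuming equal numbers.

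**Assumptions, not in the document.** ICC between patients of one acupuncturist from 0.01 to 0.10; two-sided 5% level; 80% power; one binary physician factor split 13/14; a continuous outcome in SD units.

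**Step 1: design effect.** DEFF = 1 + (m − 1) × ICC = 1 + 73.07 × ICC. Effective sample size = 2000/DEFF, and it cannot exceed 27/ICC however many patients are added.

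**Step 2: false-positive rate if the acupuncturist is ignored.** The test statistic is too large by √DEFF, so the true rejection rate of a null factor is 2 × [1 − Φ(1.96/√DEFF)].

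**Step 3: detectable difference if the acupuncturist is respected.** (t.975 + t.80) × √{[ICC + (1 − ICC)/m] × (1/13 + 1/14)}, with 27 − 2 = 25 degrees of freedom. The multiplier is 2.060 + 0.856 = 2.916, and 1/13 + 1/14 = 0.1484. At ICC 0.05, for example: 0.05 + 0.95/74.07 = 0.0628; √(0.0628 × 0.1484) = 0.0965; × 2.916 = 0.28 SD.

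| ICC (assumed) | DEFF | Effective n | Ceiling 27/ICC | Rejection rate, nominal 5% | Detectable difference |
|---|---|---|---|---|---|
| 0.01 | 1.73 | 1156 | 2700 | 14% | 0.17 SD |
| 0.02 | 2.46 | 813 | 1350 | 21% | 0.20 SD |
| 0.05 | 4.65 | 430 | 540 | 36% | 0.28 SD |
| 0.10 | 8.31 | 241 | 270 | 50% | 0.38 SD |

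The rejection rates apply where no term in the model absorbs any of the clustering. If part of it lies between centres, a centre term lowers them.

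**Step 4: what the patient count alone suggests.** For 2000 independent patients split evenly: (1.960 + 0.842) × √(4/2000) = 2.802 × 0.0447 = 0.125 SD.

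**Step 5: which count matters.** At ICC 0.05, ten times the patients (20,000) with 27 acupuncturists moves the detectable difference only from 0.28 to 0.25 SD. With 54 acupuncturists and the same 2000 patients it is 0.21 SD.

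**The case against.** The strongest reply has four parts.

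- **The counts are floors.** They apply to a first stage of a registry that keeps recruiting clinicians. This stands: 27 is not a fixed design value. But no higher target is set, so the plan is complete on its own terms at 27.
- **Hierarchical models are planned, and detail may sit in an analysis plan that is not shown.** The choice of covariates can be left to that document. But the article does list the levels and omits the one at which an objective's factors vary. A centre term removes only the between-centre part of the clustering.
- **The physician findings are meant as exploratory.** The wording is mixed: the abstract's methods and the Analytic approach section speak of exploring, while the objective and the conclusion speak of identifying.
- **Implementation details can vary between patients of one acupuncturist.** This is correct, so that half of the second objective is not limited to 27 units.

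Three stronger readings are tempting, and the document does not support them:

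- A reader might infer that the plan breaks its own 5–10 rule at physician level. The rule is stated for the total sample; applying it to acupuncturists extends it. Even so extended, 27 units support 27/10 = 2.7 to 27/5 = 5.4 variables, so five or fewer factors pass at the lower multiplier (5 × 5 = 25). Table 1 lists what is collected and does not say how many of those variables will be modelled.
- A reader might infer that only very large physician effects could be found. Differences of 0.20 to 0.38 SD are small to moderate. With an assumed NRS SD of 2.5 they are about 0.5 to 0.9 points, below the 2-point threshold in the Effective rate section (a within-patient threshold, so the comparison is only indicative).
- A reader might extend the point to centre factors as an objective. The second objective names implementation and physicians, not centres.

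**Conclusion.** The concern holds in a limited form. Physician factors are a stated objective, the minimum of 27 acupuncturists is not justified by those factors, and the models as written do not carry the acupuncturist as a level. Followed literally, a nominal 5% test of a null physician factor would reject about 14% to 50% of the time for ICC 0.01 to 0.10, less if a centre term absorbs part of the clustering. A correct test detects about 0.20 to 0.38 SD for ICC 0.02 to 0.10, against an apparent 0.125 SD.

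These sizes rest on assumed ICCs, equal numbers of patients per acupuncturist, a near-even split of the factor, and recruitment at the minimum. The direction needs only some correlation within acupuncturist. The design is not shown to be incapable of studying physician factors; its information on them is set mainly by the number of acupuncturists, and the models should reflect that.

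**What to change.** - **Analytic approach:** include acupuncturist, nested in centre, as a level in every model that contains physician factors. Test those factors with acupuncturist-level degrees of freedom: about 25 for one factor at the minimum of 27, and fewer if centres enter as fixed terms (27 − 9 − 1 = 17).
- **Sample size:** state that precision for physician factors depends on the number of acupuncturists actually recruited and not on the 2000 patients. Label the physician part of the second objective exploratory if only the minimum is reached.
- **Centre attributes:** with 9 centres and no centre objective, use them for adjustment or description.

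The cost is wording and model specification. The data are already collected, and no extra patients or acupuncturists are needed. The price is wider intervals and a weaker stated claim on physician factors.

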### Recruitment

Through academic conferences of the World Federation of Acupuncture and Moxibustion Societies (WFAS) and Chinese Association of Acupuncture-moxibustion (CAAM), we will attract more physicians. In the recruited centers, recruitment announcements will be launched to help patients know more about the program. Moreover, recruiting more clinicians to register on the platform is an important way that can be conducted on the website (www.amreg.org).

### Data elements and collection methods

All information will be collected through a specific network platform for acupuncture therapy and put on record in a paper version (http://www.amreg.org/). The main data elements include information of medical centers and acupuncturists, characteristics of patients with CLBP, acupuncture operation details, outcomes and safety information. Informed consent requires scanning and uploading. The names of diseases related to chronic back pain are identified by International Classification of Diseases (ICD-10,2010 Version) [37]; TCM syndromes are confirmed by Classification and codes of diseases and *ZHENG* of traditional Chinese medicine (GB/T 15657–1995) [38]. The acupuncture point vocabulary adopts the WHO Standard Acupuncture Point Locations in the Western Pacific Region (A WPRO Publication, 2008) [39]. All data elements will be collected using the established terminology specifications, data dictionaries.

Most of the data use structured information entry, allowing free text entry to a certain extent. Platform support Pinyin code retrieval and input and fuzzy matching input to ensure the standardization of registration information and facilitate the statistical analysis of data. Under the premise of ensuring the necessary information, entries should be as little as possible to minimize the burden on clinicians. Specific entries and variables are available in Table 1.

**Table 1 Tab1:** Metadata of main items and variables

Major data sources	Main items	Property	Main variables and labels
Medical Centre	Institutional background	Indispensable	Medical Organizations, Location and hospital attributes, Medical institution level
	Registration of contribution	Indispensable	Number of recruited practitioners, Number of enrolled patients
Physicians	Demographic Information	Indispensable	Name, Age, Gender, Place of residence, Contact information, Educational background
	Practitioner background	Indispensable	Medical Organizations, Years of employment, Professional qualification (senior or intermediate professional title)
Patients	Demographic Information	Indispensable	Name, Age, Gender, Nationality, ID number, Residence, Occupation, Marriage status. Educational Qualifications, Contact information
	CLBP Information	Indispensable	Visit date, Chief complaint, Course of disease, Location of pain, Characteristics of pain, causes of pain aggravation, Medical history, Causes of pain relief, Back function, Concomitant symptoms, History of acupuncture and Reception, auxiliary examination
	Diagnosis information	Indispensable	Disease diagnosis, Syndrome differentiation of TCM etiology and meridians, Complicating disease
	Lumbar imaging	Optional	X ray, CT examination, Magnetic Resonance Imaging
	Informed Consent	Indispensable	NA
Acupuncture treatment process	Acupuncture rationale	Indispensable	Acupuncture date, Acupuncture style, Acupoint selection principle, Operation of acupoints
	Acupuncture details	Indispensable	Response elicited, Needle retention time, Needle stimulation, Needle type (gauge, length), Adjunctive therapy, Needle parameter, Co-intervention
	Acupuncture regimen	Indispensable	Number of treatment session, Frequency of treatment
	Combined therapy	Indispensable	Pharmacotherapy, Non-pharmaceutical therapy, Other acupuncture type
Outcomes	Effectiveness evaluation	Indispensable	NRS, ODI, Effective Rate
	Safety evaluation	Indispensable	Adverse events
	Follow up	Indispensable	Disease status (Recurrence, Lower back pain related surgery, Seeking other treatments)

*CT* Computed tomography, *NA* Not applicable, *NRS* Numeric rating scale, *ODI* Oswestry disability index, *TCM* Traditional Chinese Medicine

Considering the characteristics and clinical practice of acupuncture therapies, we referenced Standards for Reporting Interventions in Clinical Trials of Acupuncture (STRICTA) [27] to building data dictionaries and frameworks. Structured, standardized, and logical metadata will be accumulated to reflect the real clinical process of acupuncture treatment for CLBP. Baseline demographic data, CLBP characteristics, patient-centered outcomes of the effectiveness and safety will be truthfully recorded. Specific data element entry and minimum dataset in the register can be found in Table 2. Acupuncture treatment and combined treatment should be recorded at each visit. Changes in symptoms, ODI, and NRS scores were recorded before and after treatment for effectiveness evaluation.

**Table 2 Tab2:** Timetable for data collection

Data elements	Therapeutic Session					Follow-up Period			
	Minimum treatment^a^			…	Last Visit	Minimum follow-up^b^			…
	First Visit	Second Visit	Thirdly Visit			Week 1	Week 12	Week 24	
Demographic information	✓								
CLBP information	✓	✓	✓	✓	✓				
Diagnosis	✓								
Lumbar imaging	✓								
Informed Consent	✓								
Acupuncture rationale	✓								
Acupuncture details	✓	✓	✓	✓	✓				
Acupuncture regimen	✓								
Combined therapy	✓	✓	✓	✓	✓				
Numerical Rating scale (NRS)	✓				✓	✓	✓	✓	
Oswestry Disability Index (ODI)	✓				✓	✓	✓	✓	
Adverse event	✓	✓	✓	✓	✓	✓	✓	✓	
Disease status						✓	✓	✓	✓

^a^The number of acupuncture treatments shall be no less than three times, ^b^No less than three follow-up visits

